#### Objectively measured sitting and physical activity

The activPAL™ micro device will be worn on the thigh 24 h/day for 7 days. It will be made waterproof using a nitrile sleeve and waterproof medical dressing. This device will assess a variety of aspects of behaviour including sitting, standing and stepping time (total and light and moderate-to-vigorous), prolonged sitting and standing, number of steps and number of transitions from sitting to an upright posture. These variables will be calculated daily (i.e., across all waking hours) and during work hours only. Participants who provide an adequate number of valid days will receive a £10 voucher at the end of each data collection time point. The activPAL is commonly used in sedentary behaviour and physical activity research [40] and has been found to be a valid and reliable measure of sitting, standing, stepping and postural transitions in adults [41–43]. The activPAL data will be cleaned and processed using a previously published automated algorithm [44].

A wrist-worn accelerometer will also be worn on the non-dominant wrist 24 h/day for 7 days. Time spent in different intensities of physical activity as well as sleep duration and other sleep variables such as efficiency will be calculated.

Participants will be asked to complete a short log each day to note the time they went to bed, went to sleep, woke up and got out of bed each day, work times, as well as recording any periods throughout the day if they removed the devices.

#### Self-reported lifestyle behaviours

Participants will be asked to complete an adapted version of the Occupational Sitting and Physical Activity Questionnaire [45], an adapted version of the past day recall of sedentary time questionnaire, which asks about sitting outside of work in certain contexts [46], as well as estimate the hours they spend sitting and breaking up sitting as part of their job [47]. Participants will be asked to estimate the percentage of their working day that they spend at their desk space and their office space.

Dietary behaviours and alcohol intake will be assessed using questions from the Whitehall II study [48]. Information on smoking status (current smoker, past smoker, non-smoker) will also be gathered by self-report.

Self-report sleep duration and quality will be assessed using the Pittsburgh Sleep Quality Index [49].

#### Demographic, medical history and medication

During their baseline visit, participants will be asked their age and date of birth, ethnicity, education level, current job role and pay grade, working site, working hours, length of time in post, number of people in their office and department, postcode and household composition. At each follow up visit, participants will be asked if there has been any change in these aspects.

Details of any history of disease or injuries that may indicate an inability to participate in the study will be measured. If needed, results will be reviewed to define eligibility. Medication will also be recorded.

#### Anthropometrics and blood pressure

Height will be measured in centimetres (cm), to 1 decimal place, using a Leicester portable height measure. Waist circumference will be measured using a standard anthropometric tape measure, with the tape measure being placed around the abdomen midway between the uppermost border of the iliac crest and the lower edge of the chest (thorax) formed by the bottom edge of the rib cage. A reading in cm, to 1 decimal point, will be taken when the tape is snug, but not compressing the skin. Weight, in kilograms (kg), and body composition will be measured using a Body Composition Analyser. Participants will remove shoes, socks and heavy outerwear clothing and ensure their pockets are empty before stepping on to the scales. Body mass index (BMI) is calculated by the scales as kg/m^2^. Blood pressure (BP) will be assessed using an Omron automated blood pressure monitor (Omron Healthcare Europe). Participants will be asked to sit quietly and relax prior to having their BP measurements taken and three readings will be taken, with the average of the last two readings used in the analyses.

#### Biochemical assessments

The Quo-Test® HbA1c Analyser (point-of-care device; EKF Diagnostics, Cardiff, UK) will be used to measure glycated haemoglobin. Additionally, we will use the Cardiochek® PLUS point-of-care analyser (PTS Diagnostics, IN, USA) to measure circulating cholesterol (total, HDL, LDL), triglycerides and glucose. Capillary blood samples will be taken from each participant using the finger prick method. The CardioChek® PLUS system, which is a portable hand-held device that requires between 15 and 40 μL (millions per microliter) of blood taken using a finger-stick, will be used for these measurements. No blood will be stored and all blood contaminated testing sticks will be deposed of appropriately. Participants will be asked to fast (no food or drink except water) for at least 10 h prior to the blood tests. All participants will receive feedback on these results.

#### Work-related measures

Job performance [50] and job satisfaction [51] will be measured using single-item 7-point likert scales. Work engagement (characterized by vigour, dedication, and absorption) will be measured using the Utrecht Work Engagement Scale [52]; a multi-item 7-point likert scale. The Need for Recovery Scale [53] will be used to measure occupational fatigue. Musculoskeletal symptoms will be assessed using the Standardised Nordic Questionnaire [54]. Work load and relations will be assessed using the demands, control and support scales from the Health and Safety Executive Management Standards Indicator Tool using a 5-point likert scale [55]. Sickness presenteeism will be assessed by the validated 8-item Work Limitations Questionnaire [56] which asks participants to rate on a six-point Likert scale how their health has affected aspects of their work in the past 2 weeks. Data on sickness absence will be collected using both self-report and from employer records and include frequency and duration of self-certified and certified sickness. Reasons for sickness absence will also be recorded. Data on sickness absence will be collected for 12 months prior to the intervention and for the 24 months of the intervention period.

#### Social norms, cohesion, support and strategies for sitting less

Organisational social norms will be assessed using eight items (e.g., ‘My workplace is committed to supporting staff choices to stand or move more at work’) on a 5-point Likert [25]. To capture the presence and extent of cohesion, cooperation and community in workplace teams the ‘social community’ sub-scale of the Copenhagen Psychosocial Questionnaire-II [57] will be used. This sub-scale uses three 6-point Likert scale items. Participants will be asked about the support they have received from the organisation, manager, colleagues and family for sitting less and moving more often [58]. Participants will be asked to report the frequency of any strategies they have used to sit less and move more often [58].

#### Mental health, well-being and quality of life

Health-related quality of life will be assessed using the EQ5D-5 L [59]. Anxiety and depression will be measured using the Hospital Anxiety and Depression Scale [60]. Stress will be measured using the Perceived Stress Scale [61]. Emotion will be assed using the Positive and Negative Affect Schedule which comprises two mood scales (positive and negative) [62]. Wellbeing will be measured using the World Health Organisation-Five Well-Being Index (WHO-5) [63].

#### Physical and mental fatigue

The Fatigue Scale [64] will be used to measure fatigue severity. The Fatigue Scale is one of the most widely used measures assessing fatigue and includes 11 items, seven assessing physical fatigue and four assessing mental fatigue. Responses to items are measured using a 4-point Likert-scale.

#### Health-related resource use

The health-related resource use will be based on a variant of the Client Service Receipt Inventory [65] and will include services that this population are likely to utilise such as GPs and Practise nurse appointments, occupational health visitors and other professionals that are deemed appropriate.

#### Workplace and workplace champion characteristics

At baseline each cluster will be asked to complete a short audit of their work environment. Basic information about each workplace champion in the intervention clusters will be collected at baseline e.g., gender, age, job role, length of experience being a workplace champion.

#### Process evaluation

The process evaluation methods will be a mix of questionnaires, interviews, focus groups and direct observation. The process evaluation will be used to understand: the participants’ experiences of the intervention and its different components; any discrepancies between expected and observed outcomes; the influence of intervention components and context on the observed outcomes; sustainability; the extent of any contamination between intervention and control; and, any unexpected events arising from participation. Completion of education and attendance at coaching sessions will be recorded. Self-report questionnaires provided to study participants will evaluate their opinions of the various intervention components (e.g. education, coaching, self-monitoring, workstation). Interviews and focus groups with study participants (sub-sample) will further examine engagement in the various components of the intervention, along with any barriers or facilitators to participating in the various components. Focus groups with workplace champions will further examine the intervention implementation and the champions’ experiences of delivery. All interviews and focus groups will be audio-recorded and transcribed verbatim.

Throughout the intervention we will monitor the fidelity of the intervention implementation using the Normalisation Process Theory framework [66] in line with guidance from the National Institutes of Health Behaviour Change Consortium and the DESMOND collaborative. Observations or recordings (via voice recorder) of sessions (e.g., coaching) will take place in both intervention arms to assess whether the content was delivered as expected and receipt of the intervention by attendees. During the observations a case report form will also be completed. The case report form will combine an ‘adherence measure’ to capture delivery (mode of delivery (dose)/duration/content) and use of resources (materials/activities). The structured observation tool will assess facilitator delivery of prescribed behaviours and behaviour change techniques. The case report form will also contain specific objective ‘receipt’ measures and will likely include examples related to how well the participants understand the content and engage in the session.

Observations in the office clusters will also take place in a random sample of offices in both intervention arms at several time points during the intervention period. Each observation will be performed over one whole working day. This observation work will be guided by the four domains of the Normalisation Process Theory and an observation guide will highlight the types of behaviours of focus, such as: use of height adjustable workstation, sitting and standing time, engagement with colleagues, walking/standing meetings as well as office structure, posters displayed. Practically, the observation work will include keeping structured field notes and collating relevant documentation for further context and insight, and may include informal discussions with office workers and workplace champions. A random sample of control offices will also be observed to judge contamination and other practices that may impact on our behaviours of interest.

### Statistical analysis

#### Primary and secondary outcomes

The aim of the primary analysis is to investigate the impact of the multi-component intervention (SMART Work & Life), with and without a height-adjustable workstation, on objectively measured daily sitting time compared to usual practice at 24-month follow-up. The primary outcome analysis is powered to detect a significant difference in sitting time of 60 min/day at 24 months. However, discontinuation of the study due to futility will be considered in a formal interim analysis at 12 months. An Independent Data Monitoring Committee (DMC) will be convened to review the primary outcome at 12 months. The conditional probability of the final study results being statistically significant given the data observed at 12 months will be calculated and the DMC will make a recommendation based on this and other important factors (i.e. trial conduct, data quality, participant retention) of whether or not to continue follow-up until 24 months. If the DMC decide the data from the interim analysis at 12 months provides satisfactory evidence to continue, the trial will continue to follow-up participants to 24 months. Furthermore, only if both arms are determined to be futile at the interim analysis stage will the trial be stopped early.

The primary analysis will be performed using a linear multilevel model with sitting time as the outcome variable. Levels to indicate the clustering of workers within office sites, a categorical variable for randomisation group as the explanatory variable (control will be the reference group and will be compared to intervention 1 and intervention 2), and terms for the stratification factors (area and cluster size), baseline values and device wear time will be confounders. In these linear multilevel models, office clusters will be incorporated as a random effect to model worker heterogeneity within office sites. The structure of the variance-covariance matrix for the random effect will be assumed to be unstructured and the models will be estimated using restricted maximum likelihood. For the primary analysis, missing data will not be replaced (complete case analysis) and participants will be included in the intervention group in which their clusters were randomised irrespective of the intervention that was actually received.

The baseline characteristics of those who have complete primary outcome data will be compared with those who dropped out from the study in order to investigate differences between them.

A sensitivity analysis using multiple imputation will be performed to evaluate the impact of missing outcome data on the results obtained and to account for uncertainty associated with imputing data (full intention-to-treat analysis). Missing data will be replaced using multiple imputation methods in Stata using the MI command. The effect size will also be estimated using a per-protocol analysis, which will only include those who were compliant with the protocol and follow-up visits. Secondary outcomes, including those measured at other time-points, will be analysed using similar methodology. We will additionally assess data from all time points for the primary outcome in a single analysis using repeated measured. We will also conduct a subgroup analysis which compares the treatment effect in those clusters in which other work place health initiatives were taking place at the same time as the study compared to those where there were no such initiatives.

All tests and reported *p*-values will be two-sided. Estimates will be presented with 95% confidence intervals.

#### Process evaluation

Questionnaire data will be summarised using frequency counts and means (± SD) where appropriate. Audio-recordings of interviews and focus groups with office workers and workplace champions will be transcribed verbatim and analysed using framework analysis using the Normalisation Process Theory as the overarching framework.

#### Cost effectiveness

The economic evaluation will consist of two analyses. i) a cost-consequence analysis based on the observed results within the trial period and ii) a cost-effectiveness analysis where differences between groups in the trial will be extrapolated to the longer term where appropriate.

For both analyses, costs in both arms will be estimated from a National Health Service (NHS) and Personal Social Services (PSS) perspective (consistent with that used by the National Institute for Health and Care Excellence (NICE)) as well as a wider public sector perspective. In each analysis, the cost of the SMART Work & Life groups will include an estimate of the cost of the intervention, with and without the height adjustable desk. The cost of the intervention consists of the cost of equipment (such as desks) and the cost of training and delivery of intervention. We will estimate the cost of the equipment from manufacturer’s estimates of costs. We will also estimate the cost of training and delivery of intervention by the workplace champions.

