A review was published in 2016, and updated in 2018, summarising the effectiveness of workplace interventions for reducing sitting time at work [22, 23]. These interventions included physical workplace changes such as providing height adjustable desks to enable sitting or standing at work, pedalling workstations and treadmill desks, policy changes, information provision and counselling, and computer prompts. Providing height-adjustable workstations was the most frequently implemented intervention and was reported as the most promising for reducing sitting time at work (average reduction of 100 min/work day in the short term, 57 min/work day in the medium term) [23]. Whilst positive findings were observed, the review concluded that the quality of evidence was low to very low for most studies mainly because studies were poorly designed; for example, there was a lack of non-biased cluster randomised controlled trials, and generally small samples. They also concluded that ‘there is a need for larger cluster-randomised trials with longer term follow-up’.

To date only a handful of studies currently address these limitations [24, 25] and only one ongoing study, albeit that does not include a control group, has a follow up beyond 12 months [26]. The Stand More AT Work (SMArT Work) multi-component intervention was evaluated through a large cluster RCT with follow up at 3, 6 and 12 months [24, 27]. Although SMArT Work was successful in reducing sitting time at work et all follow up time points, results suggested that no changes in sitting outside of work were made as reductions seen for daily sitting time were similar to those observed during work hours [27]. Similarly, the Stand Up Victoria trial also observed significant changes in sitting time across the day, but findings suggested that this was also predominantly driven by workplace changes, rather than changes during non-work time [28]. To maximise the potential health benefits of reducing sitting time there is a need for interventions to take a ‘whole of day’ approach to behaviour change, and focus not only on workplace sitting time, but also on sitting outside of work.

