### Aims and objectives of the study

#### Aim

The aim of this study is to determine the long-term effectiveness and cost-effectiveness of the multi-component SMART Work & Life intervention (when provided with and without a height-adjustable workstation) for reducing daily sitting time in office workers compared with no intervention. If both interventions are shown to be effective, a secondary aim will be to determine if one intervention is more effective than the other. SMART Work & Life is a refined and extended version of the previously evaluated SMArT Work intervention [24, 27].

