##### Within-trial analysis

Within the period of the trial, we will collect resource use estimates from participant questionnaires. These questionnaires will record health related resource use as well as absence from employment. The health related resource use will be based on a variant of the Client Service Receipt Inventory and will include services that this population are likely to utilise such as GPs and Practice nurse appointments, occupational health visitors and other professionals that are deemed appropriate. Costs of resources will be calculated by applying published national unit cost estimates (e.g. NHS reference costs or Personal Social Services Research Unit costs of health and social care), where available, to estimates of relevant resource use.

A range of outcomes will be assessed in the trial including health related quality of life, measured using the EQ5D-5 L The within trial analysis will present incremental results for the primary and secondary outcomes (including EQ5D) in both intervention and control arms and will be compared with the incremental costs measured above. We will also present the results in terms of the differences in time absent from work between the groups. As there is some controversy over inclusion of productivity losses in the assessment of cost-effectiveness, the within trial analysis will be presented both with and without estimates of the cost of sickness absenteeism. This will allow decision makers to assess the importance of inclusion of absenteeism costs when deciding whether to implement the intervention.

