##### Longer term analysis

While there may be short term health benefits from reducing levels of sitting time, the longer term effects on mortality on office workers is likely to be more important. We will therefore use existing evidence that links short-term trial endpoints and longer term outcomes. While some existing evidence used covariates to adjust for confounding factors, it is not possible to assess unmeasured confounders. Therefore, we will use existing evidence to extrapolate costs and effects to a more appropriate time horizon; however, as recommended by Taylor and Elston [67] we will explain how the surrogate-final outcomes relationship is quantified and explore the uncertainty around the use of the surrogate outcome (in this case sitting time) through sensitivity analysis.

If appropriate an Incremental Cost-effectiveness Ratio for the extrapolated period will be reported using the Quality Adjusted Life Year (QALY). As with the within-trial analysis, we will conduct analyses where productivity losses are included/excluded to assess the impact on decision making. Costs and effects will be discounted at the prevailing recommended rate (currently 1.5% per annum on both costs and effects), but will be the subject of sensitivity analysis to reflect the ongoing uncertainty around appropriate discount rates for public health interventions. We will conduct probabilistic sensitivity analyses to allow a characterisation of the uncertainty around the adoption decision which we will depict using cost-effectiveness acceptability curves. Sensitivity analyses will be performed to determine the robustness of the results to altering certain assumptions such as the discount rate, inclusion/exclusion of productivity losses and the robustness of the relationship between sitting time and mortality.

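### Cost-effectiveness is part of the main aim, but the only cost per QALY named is conditional and extrapolated, although EQ-5D-5L at four visits would support a within-trial ratio

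*Protocol article*

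**What the plan says.** The Aim section opens with "The aim of this study is to determine the long-term effectiveness and cost-effectiveness of the multi-component SMART Work & Life intervention", so the economic question stands beside the effectiveness question.

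The Cost effectiveness section divides the economic evaluation into two parts. The first is "a cost-consequence analysis based on the observed results within the trial period". The second is "a cost-effectiveness analysis where differences between groups in the trial will be extrapolated to the longer term where appropriate".

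The Within-trial analysis section fills in the first part: "The within trial analysis will present incremental results for the primary and secondary outcomes (including EQ5D) in both intervention and control arms". These results are to be compared with incremental costs, with and without the cost of sickness absence. No QALY, ratio or net benefit is named there.

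The Longer term analysis section fills in the second part: "If appropriate an Incremental Cost-effectiveness Ratio for the extrapolated period will be reported using the Quality Adjusted Life Year (QALY"). It says that the evidence linking short-term endpoints to long-term outcomes is in part covariate-adjusted but leaves unmeasured confounding that cannot be assessed. It promises probabilistic analysis with acceptability curves, and sensitivity analyses on the surrogate relationship and other assumptions.

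On data, the section on mental health, well-being and quality of life states: "Health-related quality of life will be assessed using the EQ5D-5 L". It gives no separate schedule, so the default in the Measurements section applies: baseline, 3, 12 and 24 months. The Secondary objectives also list quality of life among outcomes assessed at 3, 12 and 24 months.

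**The concern.** The plan states the type of each economic analysis, and neither type secures an answer to the cost-effectiveness half of the aim. The unconditional analysis sets costs beside a range of outcomes and leaves the weighing to the reader. The analysis that would give a single ratio is optional twice over: the extrapolation is done only where appropriate, and the ratio is reported only if appropriate.

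Two things are at stake. First, if the team concludes that extrapolation is not warranted, for example because the sitting-mortality evidence is too confounded, the trial can finish without any cost-effectiveness ratio it was committed to report. Second, if extrapolation goes ahead, the only ratio depends on a non-randomised link, with no ratio from the randomised comparison to set beside it. Employers and public bodies deciding whether to pay for the programme, with or without the desk, would have no cost per QALY that rests on trial data alone.

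**Working it through.** The economic sections give no figure to reproduce. The sample-size figures concern sitting time and do not bear on this point. The check is a comparison of sections, followed by a test of whether the collected data can support the missing quantity.

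**Step 1. What is committed to.**

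| Analysis | Type stated | Conditional? | QALY named? | Ratio named? |
|---|---|---|---|---|
| Within-trial | Cost-consequence | No | No (incremental EQ5D only) | No |
| Longer term | Cost-effectiveness by extrapolation | Yes, on the extrapolation and on the ratio | Yes | Yes, for the extrapolated period |

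The number of cost-effectiveness ratios reported whatever is decided about extrapolation is therefore zero.

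**Step 2. Whether a within-trial QALY can be calculated.** Inputs: EQ-5D-5L at 0, 3, 12 and 24 months, which is 0, 0.25, 1 and 2 years (Measurements section). With straight lines between visits, the QALY over 24 months is the trapezoid area under the utility curve, a weighted sum of the four utilities. The weights are:

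- baseline: (0.25 − 0)/2 = 0.125
- 3 months: (1 − 0)/2 = 0.5
- 12 months: (2 − 0.25)/2 = 0.875
- 24 months: (2 − 1)/2 = 0.5

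They sum to 0.125 + 0.5 + 0.875 + 0.5 = 2.0 years, so the visits cover the whole follow-up with no gap to model.

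**Step 3. Whether the costs exist.** The Cost effectiveness and Within-trial analysis sections plan intervention costs (equipment, training, delivery), health-related resource use from questionnaires with published unit costs, and absence from work. The numerator is therefore already planned over the same period.

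**Step 4. Order of size.** The documents give no expected utility difference, so the following gains are assumptions. Take equal baselines and a constant gain *d* from 3 months to 24 months. The QALY gain, before discounting, is *d* × (0.5 + 0.875 + 0.5) = 1.875*d*:

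- *d* = 0.005: 0.009 QALY
- *d* = 0.01: 0.019 QALY
- *d* = 0.02: 0.038 QALY

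These gains are small, and a ratio with so small a denominator may be imprecise. That is a reason to report it with its uncertainty. The documents give no standard deviation or intraclass correlation for utility, and no variance for costs, so the width of an interval cannot be worked out.

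**The case against.** The strongest reply is that the within-trial analysis is not empty. It will present incremental EQ5D, sitting time and absence against incremental costs whatever happens to the extrapolation. A cost-consequence layout is a recognised choice for an intervention with many outcome domains, and the plan gives a reason for looking further ahead: it expects long-term mortality effects to matter more than short-term benefits. It is also open about confounding and promises to explore surrogate uncertainty. All of this stands, and it would be wrong to say that the plan offers nothing on cost-effectiveness without extrapolation. But a cost-consequence table is not a cost per QALY, and the aim is worded as cost-effectiveness. Nor can the gap be put down to the brevity of an article, because the type of each analysis is stated. A fuller plan that followed this text would still be cost-consequence within the trial.

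A reader might go further and infer that the extrapolation holds the trial difference constant and never varies how long it lasts. The text does not support that. The assumptions to be altered are given as examples ("such as the discount rate, inclusion/exclusion of productivity losses and the robustness of the relationship between sitting time and mortality"), nothing says that the difference is held constant, and an article may leave waning scenarios to a fuller plan. A fold-change in benefit from different durations would rest on a horizon, fade shapes and fixed costs that the documents do not give.

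The Background figures ("average reduction of 100 min/work day in the short term, 57 min/work day in the medium term") do not show desks losing their effect either. They are averages from a review at two lengths of follow-up, not stated to come from the same workers, for sitting at work, in evidence described there as mostly low or very low quality.

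It would also go too far to say that the EQ-5D-5L data will never feed a QALY. The plan does not say which utility data enter the longer-term model.

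**Conclusion.** The point holds in a limited form. The main aim includes cost-effectiveness, but the plan assures no cost-effectiveness ratio: the within-trial analysis is cost-consequence only, and the sole cost per QALY is conditional, extrapolated and dependent on an observational link whose unmeasured confounding the plan says cannot be assessed. The data for a 24-month cost per QALY are already planned.

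This is a gap in what the analysis commits to. It is not an error in a number, and it does not touch the primary outcome. It rests on one reading, that EQ-5D-5L follows the default four-visit schedule, which the Secondary objectives support. The utility gains in the working are assumptions that show scale only; the conclusion does not depend on them. No conclusion is drawn about how long the effect lasts or which duration the model should assume.

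**What to change.** In the Within-trial analysis section, add a 24-month cost-utility analysis:

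- QALYs as the area under the EQ-5D-5L utility curve over baseline, 3, 12 and 24 months;
- differences between each intervention arm and control adjusted for baseline utility and for office clustering;
- these differences set against the within-trial costs already planned, with and without absence costs;
- incremental cost per QALY reported with its uncertainty, whether or not the extrapolation is done.

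The cost-consequence presentation and the longer-term model can stay as they are. As an optional addition, duration of effect after 24 months could be named among the sensitivity analyses of the longer-term model; the choice of base case can be left to the sponsor.

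The cost is a few lines of text and some extra analysis, with no new data collection. The downside is that the 24-month ratio may be imprecise, or less favourable than the extrapolated one, and the report should say so.
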